##### Data analysis for Aim 3a

A descriptive analysis will be used to summarize the responses to the helpfulness scale items. Statistical assumptions will be tested to determine whether to use analysis of variance (ANOVA) or the Kruskal‒Wallis test for comparing mean scores between four groups: patients, caregivers, and interventionists (faith community nurses and visiting volunteers). Interventionists will also use anecdotal notes to report topics brought up by families that require reinforcement. These topics will be tabulated and reported to improve the intervention.

To determine the cost of the **HF**-FamPAL**home**CARE intervention implementation, all charges related to implementation are calculated. The items include the costs of personnel time for training and administering each discussion session, the materials, home/clinic visit travel, and telephone and mailing costs. Research costs related to data collection and material photocopying will be totaled and reported as study costs. The average intervention implementation cost across all families will be calculated and reported [15].

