### Design/methodology

This study uses a randomized controlled trial (RCT) design stratified by sex to determine the effectiveness and helpfulness of the **HF**-FamPAL**home**CARE bundled intervention (N = 208, 104 dyads: 104 patients and 104 family caregivers). The intervention group (52 dyads) will receive the intervention. The control group (52 dyads) will receive attention control consisting of education on general health topics that indirectly affect HF (e.g., vaccinations, handwashing). At the end of the 12-month completion period, each group received the content provided to the other group. See Fig. 1.

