#### Sample size

The power and sample size determination is based on a preliminary RCT, which revealed a moderate effect reduction in the burden of caregiving and improvements in patients’ HF-related health status [15]. With the use of G*Power v.3.1.9.7 for repeated-measures ANOVA with α = 0.05, Cohen’s d = 0.25 (moderate effect size), a power of 80%, two groups with 5 measurements, and correlations among repeated measures (0.50), a *sample size of 86 family dyads* will be needed. Our power analyses performed by this study’s statistician indicate that this sample size is sensitive enough to detect a significant difference in the study outcomes with this repeated measure design [36].

Our biostatistician’s revised precision calculation for linear mixed model analysis was based on the effect size outcomes of our HF palliative care studies. To account for an expected 20% attrition (many due to HF-related deaths), eight additional families will be recruited for each group. The calculated sample size was 86 patients, with an additional n = 18 for the expected 20% attrition rate (total sample N = 208; 104 patients and 104 caregivers) for this study. In this analysis, the random and fixed effects and quarterly repeated measures also add power.

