#### Data collection for Aims 3a and 3b

*For Aim 3a,* each patient and family member independently rated the helpfulness of each intervention component via a 15-item Likert-type scale at 6 and 12 months after the completion of the **HF**-FamPAL**home**CARE intervention. The participants will rate their agreement with statements, with response options ranging from 1 (strongly disagree) to 5 (strongly agree). Sample statements include *“The nurse and volunteer prepared me for home HF care,” “I was comfortable during the discussion with the nurse/visitor,”* and *“I know ways to reduce breathlessness.”* Descriptive analysis will be used to evaluate the responses on the helpfulness scale. The nurse interventionists and visiting volunteers will rate the same helpfulness scale at 6 and 12 months following the **HF**-FamPAL**home**CARE intervention.

*Aim 3b: Focus group data collection.* The Principal Investigator (PI) and Co-Investigator (Co-I) are experienced in focus group research methods and working with families managing HF [47]. We will conduct 4 to 6 focus groups across West Virginia counties, each consisting of 3 to 5 rural stakeholders, such as church leaders, patients, and caregivers. These sessions will be held at rural sites, with the option of using a secured ZOOM for recording encrypted discussions and enabling participation from other rural leaders.

The PI and Co-I will facilitate discussions, starting with questions such as *“How can we collaborate to develop a 10-year plan for maintaining rural volunteers and continuing home care implementation?”* and *“What are the facilitators of and barriers to sustaining the HF-FamPALhomeCARE intervention in rural Appalachia?”* The same broad questions with prompts will guide all focus group discussions. The PI and Co-I will observe group dynamics to ensure that everyone participates and will ask probing questions for clarification and deeper insights.

The discussions will be audiotaped and transcribed, ensuring that no individual participants’ identities are disclosed. Each session will last approximately 60 to 90 min. Data saturation is achieved when no new topics emerge, with experts indicating that 99% of all new concepts typically emerge by the 20th participant [48]. All group data will be transcribed together.

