## Limitations and alternatives

The population of West Virginia is 93% Caucasian, but we have successfully enrolled underrepresented minorities in past studies. We anticipate a 20% attrition rate, primarily due to HF-related deaths. In previous studies, few caregivers withdrew after patient death, indicating that they were able to contact study nurses. To increase enrollment, program brochures are distributed in local churches by lay ministers and faith community nurses. Additionally, healthcare providers involved in HF patient discharges or ER visits may refer families to the program. Finally, the West Virginia University (WVU) integrated data repository (IDR) will be used for enrollment, as it has proven helpful for screening patients with HF across WV counties in the PI’s previous trials.

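### Aim 3a gives Kruskal-Wallis the job of comparing mean helpfulness scores; with unequal spread near the top of a 1 to 5 scale it can reject when the means are equal

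*Protocol article*

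**What the plan says.** The section Data analysis for Aim 3a plans a descriptive summary of the helpfulness items and then a formal comparison. "Statistical assumptions will be tested to determine whether to use analysis of variance (ANOVA) or the Kruskal‒Wallis test for comparing mean scores" is the selection rule, and the comparison is across four rater groups: patients, caregivers, faith community nurses and visiting volunteers. No separate interpretation is given for the rank test.

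The section Data collection for Aims 3a and 3b describes the instrument as "a 15-item Likert-type scale at 6 and 12 months", with "response options ranging from 1 (strongly disagree) to 5 (strongly agree"), so a rater's average cannot exceed 5. The raters among families are those in the intervention arm: "The intervention group (52 dyads) will receive the intervention". The number of nurses and volunteers is not stated, nor is any expected mean or spread of the scores. Table 1 phrases Aim 3a as a comparison of ratings and lists it under the secondary aim.

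**The concern.** ANOVA compares means. Kruskal-Wallis compares mean ranks, and its null distribution comes from exchanging ranks between groups, so its null is that all groups share one distribution. It can be read as a comparison of location, and hence of means, only when the groups have the same shape and spread. The plan reaches for it when assumption checks fail, and unequal spread is one of the usual failures. In that case the change of test also changes the question, while the text keeps the same stated target.

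A scale capped at 5 makes this more than a technicality. If ratings gather near the top, a group with wide spread has many raters at the cap and a long lower tail. A group with narrow spread and the same mean has fewer at the cap and a higher floor. Their medians and ranks then differ although their means do not.

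At stake is a statement that families and interventionists differ in mean helpfulness when they may not. The article also compares the helpfulness results with the focus-group themes on sustainability, so such a statement could carry into that planning.

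**Working it through.** **Figure to reproduce.** None: the article gives no sample size, power or error rate for Aim 3a.

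**Inputs from the article.** Scale 1 to 5, 15 items, four rater groups; 52 patients and 52 caregivers before attrition. With 20% attrition, 52 × 0.8 = 41.6, about 42 per group; from the calculated 86 dyads, 86 / 2 = 43.

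**Assumptions.** The 5% level (the article gives it only for the sample size calculation); 5, 10 or 20 nurses and as many volunteers; common mean 3.0 to 4.6; SDs 0.3 to 0.95. No assumption tests are named, so the rule was taken as Kruskal-Wallis if Shapiro-Wilk on residuals or Levene gives p < 0.05, otherwise ANOVA.

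**Why equal means can give different ranks.** Model a rater's average as 1 + 4·Beta(a, b), rounded to 1/15. With μ = (mean − 1)/4, v = (SD/4)² and k = μ(1 − μ)/v − 1, set a = μk and b = (1 − μ)k. At mean 4.5, μ = 0.875.

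- SD 0.8: v = 0.04, k = 0.109375/0.04 − 1 = 1.734, a = 1.52, b = 0.22. Median 4.93; about 40% of raters at exactly 5.
- SD 0.5: v = 0.015625, k = 6.0, a = 5.25, b = 0.75. Median 4.67; about 10% at exactly 5.

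The means are equal, but a rater from the first group outranks one from the second with probability about 0.63 (ties split).

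**Two groups, 42 each, independent raters, equal means.**

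| SDs | Kruskal-Wallis, mean 4.2 | Kruskal-Wallis, mean 4.5 |
|---|---|---|
| 0.6 v 0.5 | 7% | 10% |
| 0.7 v 0.5 | 11% | 27% |
| 0.8 v 0.5 | 20% | 52% |

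With equal SDs Kruskal-Wallis stays near 5%. The unequal-variance t-test stays at about 4% to 6% for SDs of 0.7 or 0.8 v 0.5.

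**Four groups, two-stage rule, equal means.** 52 patients, 52 caregivers and m raters in each interventionist group; 2,000 simulated trials per setting (simulation standard error at a rate of 50%: √(0.25/2000) = 1.1 points). SDs are in the order patients, caregivers, nurses, volunteers.

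| SDs | Largest/smallest | Mean 4.3, m = 10 | Mean 4.5, m = 5 | Mean 4.5, m = 10 | Mean 4.5, m = 20 |
|---|---|---|---|---|---|
| 0.5/0.5/0.35/0.35 | 1.4 | 3% | 2% | 5% | 9% |
| 0.6/0.6/0.3/0.3 | 2.0 | 5% | 4% | 12% | 34% |
| 0.7/0.5/0.3/0.3 | 2.3 | 12% | 21% | 32% | 51% |
| 0.8/0.5/0.3/0.3 | 2.7 | 24% | 46% | 60% | 75% |

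With equal SDs the rate is 4% to 6% at every mean. At mean 3.0 with unequal SDs it is 1% to 3%. With 43 instead of 52, the m = 10, mean 4.5 column becomes 5%, 14%, 30% and 54%. At means of 4.3 or more the checks fail in at least 95% of samples, so Kruskal-Wallis is nearly always the test used.

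**Sensitivity to the model.** Simulating 15 ordinal items from a latent normal, with within-dyad correlation 0 or 0.4, gives the same pattern at mean 4.5 with m = 10: 3% to 5% for SDs of about 0.57/0.57/0.40/0.40, 19% to 23% for 0.70/0.57/0.30/0.30, and 47% for 0.80/0.57/0.30/0.30.

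**Alternatives that target means.** Four-group Welch ANOVA gives about 4% to 8% in nearly all settings with 10 or 20 raters per interventionist group, and 5% to 15% with 5. For patients versus caregivers with within-dyad correlation 0.4, the two-sample Welch test rejects only about 1% to 2%, because it ignores the pairing; a paired mean difference rejects 4% to 6%.

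**The case against.** **Reading of the text.** Table 1 asks only for a comparison of ratings, which a rank test does provide. The phrase about mean scores could also refer to each rater's average over the 15 items. That reading is possible, but "comparing mean scores between four groups: patients, caregivers, and interventionists (faith community nurses and visiting volunteers") more naturally means a comparison of group means. The article does not say how a significant rank test would be worded, so a false report is a risk and not a stated intention.

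**Not a false alarm in every sense.** In the worst settings the groups really do differ: 40% against 10% at the cap is a real difference in ratings, and Kruskal-Wallis is right to find it. This stands, and it is why the conclusion should be phrased as a difference in distribution. The error lies in calling it a difference in means.

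**Frequency.** A reader might infer that the plan will often declare a difference when mean helpfulness is equal. The documents do not support that. They give no means, SDs, share at the ceiling or interventionist numbers. At an SD ratio of about 1.4, with means of 4.3 to 4.5 and 5 or 10 raters per interventionist group, the rate was about 1% to 6%; the highest in any setting tried at that ratio was 13% (mean 4.6, 20 raters each). With 5 raters per interventionist group it can stay below 5% even at a ratio of 2. The two-group rates above are larger for a given SD ratio, but the article does not plan that pairwise test.

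**Detail left elsewhere.** Which assumption checks are used may fairly sit in a fuller document, and the rule simulated here is assumed. The pairing of a rank test with mean scores, however, is stated in the article itself.

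**Conclusion.** The point holds in a limited form. The article assigns Kruskal-Wallis to a comparison of mean scores, which it does not make when spread or shape differs, and the bounded scale makes such differences plausible. Under assumed inputs the four-group false-positive rate for equal means ranges from below 5% to about 50% or more. The high end needs both a largest-to-smallest SD ratio above 2 and a mean near 4.5. The mechanism is certain; its size in this trial is unknown, and frequent error is not shown. Importance is low: the aim is secondary, has no hypothesis or power statement, and the items are also summarised descriptively.

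**What to change.** In Data analysis for Aim 3a:

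1. If Kruskal-Wallis is kept for the four rater groups, state its conclusion as a difference in the distribution of ratings, not in mean scores.
2. Where a mean difference is wanted, estimate it without a preliminary assumption test. For patients versus caregivers, give a 95% interval for the within-dyad (paired) mean difference. This allows unequal variances and respects the dyads; a two-sample Welch interval would ignore the pairing.

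This keeps nurses and volunteers in the comparison that Aim 3a names.

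The cost is a sentence or two of text, one more estimate, and a less direct reading of the four-group p-value. The paired interval uses only dyads in which both members rated. The article also describes the rating forms as anonymous, so pairing needs a coded dyad link on them; without one, item 1 can still be done.

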##### Data analysis for Aim 3b

We will conduct focus group research with rural stakeholders and our interventionists to create a 10-year plan for sustaining rural volunteers, continuing bundle implementation, and managing the administrative aspects of the program. Each focus group begins with an expression of gratitude for discussing the sustainability of the intervention bundle.

Content analysis will be used to transcribe discussions into written narrative data, with qualitative data analysis conducted continuously alongside data collection [50]. The PI and Co-I code the data after all focus group sessions, maintaining an audit trail of key decisions. Transcribed notes will be anonymized, and qualitative software will facilitate data management. Themes are compared with the social support framework, quantitative results, and Aim 3a helpfulness ratings to identify additional facilitators or barriers to sustainability [51].

To maintain the rigor of qualitative data analysis, the PI and Co-I independently code transcribed data and then reconcile categories. Themes are labeled via participants' words, and consistent questions across groups enhance credibility. New themes will provide insights into data dependability. Investigators will ensure 100% agreement on codes to avoid bias. Themes represent sustainability planning factors and are compared with quantitative measures, helpfulness results, and anecdotal notes from faith community nurses and visiting volunteers. Member checks involve rural stakeholders reviewing sustainability reports to ensure accuracy. These methods aim to achieve multiperspective 10-year planning solutions.

## Human subject protection and management of risks to subjects

Subject enrollment will occur across West Virginia and neighboring rural counties. Research staff will be trained and certified in Human Subjects Protection. The participants will provide consent, and a HIPAA waiver will allow access to the recruitment list. Confidentiality will be maintained through WVU policies, with measures in place to prevent breaches. Data management procedures include securely storing questionnaires and consent forms, and electronic data are stored on a firewall-protected server with daily backups.

## Data and safety monitoring

All adverse events will be reported to the IRB and the National Institute of Nursing Research (NINR). The PI and Co-Is review adverse events within 2 business days. Adverse events must be reported to the IRB within 3 business days. The PI will report IRB actions to the NINR within 2 business days. Any changes or amendments to the protocol or consent form will be reported to the NINR within 3 business days of IRB approval. Any change in scope will be submitted to the NINR for approval before implementation. Adverse events will be documented and reported to the NINR through the annual reporting system.

The Safety Monitoring Committee (SMC) for this RCT includes two independent experts. The SMC reviews each potential adverse event (AE) in real time and biannually. They provide guidance on interim analyses and stopping guidelines and address ethical issues related to palliative care, study safety, and research risks. Recommendations and actions will be reported to the IRB and NINR.

## Limitations and alternatives

The population of West Virginia is 93% Caucasian, but we have successfully enrolled underrepresented minorities in past studies. We anticipate a 20% attrition rate, primarily due to HF-related deaths. In previous studies, few caregivers withdrew after patient death, indicating that they were able to contact study nurses. To increase enrollment, program brochures are distributed in local churches by lay ministers and faith community nurses. Additionally, healthcare providers involved in HF patient discharges or ER visits may refer families to the program. Finally, the West Virginia University (WVU) integrated data repository (IDR) will be used for enrollment, as it has proven helpful for screening patients with HF across WV counties in the PI’s previous trials.

## Discussion

The aim of this mixed methods randomized controlled trial (RCT) is to test the integrated nurse-led intervention bundle of **HF**-FamPAL**home**CARE and to assess the bundled intervention helpfulness as well as develop plans for maintaining sustainable relationships with our rural stakeholder network, visiting volunteers, and the Faith Community Nurse Network of rural WV.

Notably, patients with HF and their caregivers in rural settings lack sufficient guidance for managing HF symptoms. Appalachians have expressed their desire to have access to health care and to die at home [8]. Thus, the **HF**-FamPAL**home**CARE intervention has been designed to address these issues by using Appalachian faith community nurses to engage families in culturally sensitive skills to manage HF symptoms, anxiety and depression and to hold discussions of their family’s EOL care preferences [52]. The home EOLPC discussed with families is based on HF provider recommendations and evidence-based national clinical guidelines for end-stage HF [14]. EOLPC discussions have resulted in care aligned with patient preferences, positive family evaluations of healthcare, and significantly fewer unwarranted HF hospital readmissions [53].

This R01 study supports research to improve health equity by improving access to health services and addressing disparities related to SDoH in underrepresented rural Appalachia [4, 8, 9]. Designing and testing practical sustainable approaches using available rural resources will address a prevalent disease, support EOLPC preferences, reinforce older adults’ functional health and HF home caregiving skills, and provide social support. Engaging rural stakeholders in recruitment and implementation and designing sustainability plans can result in continuing research on health and EOLPC and targeting disparities related to SDoH among the 26.3 million people living across Appalachia [9]. The long-term impact will be the creation of pragmatic strategies for other rural Appalachian states [54].

The PI and research team will adhere to the NIH Policy on Dissemination of NIH-Funded Clinical Trial Information. Clinical trial details and study results will be promptly updated and made publicly accessible via ClinicalTrials.gov, a database managed by the National Library of Medicine (NLM) of the National Institutes of Health (NIH). The trial results will be submitted within one year of the trial's primary completion date.

## Conclusion

The scientific merit of this study is that it is based on the social support framework, practices, and beliefs of the underserved rural Appalachian population, and the empirically verified research results from our series of preliminary HF palliative care studies. Our interventions address the needs of patients and family members while incorporating cultural traditions. Key factors for successful implementation and sustainability include the involvement of local nurse interventionists, the engagement of rural stakeholders, and the use of local resources to address health disparities and strengthen communities. This project will provide insights into sustaining volunteer programs in underserved Appalachian areas.

## Data Availability

No datasets were generated or analysed during the current study.

## Abbreviations

HF: Heart failure
EOLPC: End-of-life palliative care
HF-FamPALhomeCARE: Family home palliative care intervention for heart failure
IRB: Institutional Review Board
WV: West Virginia
SMC: Safety Monitoring Committee
AHA: American Heart Association
CONSORT: Consolidated Standards of Reporting Trials
SPIRIT: Standard Protocol Items: Recommendations for Interventional Trials
